#### Analysis of secondary endpoints

For both interventions, the secondary endpoints will be compared by the *t*-test if normally distributed, by the Mann–Whitney *U* test if similarly shaped but are not normally distributed continuous data, by chi-square tests for categorical data or by the log-rank test for time-to-event data, as appropriate. Since this is a feasibility study we will not have enough power to test for non-inferiority. Estimates of effect size and corresponding confidence intervals will be provided. Exploratory analyses of endpoints adjusted for possible confounders will be performed using linear or logistic regression or Cox proportional hazards models, as appropriate. Prognostic accuracy will be assessed by receiver operating characteristic curve analysis and by calculating sensitivity, specificity, positive and negative predictive values and likelihood ratios for medical and biopsychosocial risk assessments.

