#### Intervention B

The triage decision in the ED is based on an interdisciplinary biopsychosocial and functional risk assessment by the treating physician (for medical risk) and the ED nursing team (for biopsychosocial risk) (Figure 3). Hospitalization criteria in the control group include: 1. severe illness, high fever (≥39°C), costovertebral angle tenderness or flank pain; 2. inability to take oral medications or fluids; dehydration; 3. questionable patient compliance; 4. complications of pyelonephritis and 5. co-morbidities. In the ProADM group, the subjective admission criterion 1 (severe illness, high fever, costovertebral angle tenderness, severely impaired health) is omitted (simple UTI) or replaced by objective ProADM cutoffs for patients with febrile UTI/pyelonephritis. In patients with simple UTI, we do not expect the ProADM levels to provide sufficient prognostic information and therefore do not include ProADM in their admission criteria. A standardized score (the post-acute care discharge score, PACD) [45] is used to stratify all patients as low or high risk for subsequent rehabilitation and care. The final triage decision is a consensus by physicians, nurses and patient (or relatives). If a consensus cannot be reached, the patient’s preference has priority.

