**Figure 4 F4:**
[figure not shown]
**Risk assessment during hospitalization - site-of-care decisions (ProADM on day 3).** ICU: intensive care unit; PACD: post-acute care discharge score; SPI: *Selbstpflegeindex* self-care deficit score; UTI: urinary tract infection.

Levels of ProADM are measured on admission and on day 3. ProADM cutoff tertiles derived from patients with LRTI will be used for severity assessment [41]: <0.75 nmol/l; 0.75 to 1.5 nmol/l; >1.5 nmol/l. Physicians receive detailed information on how to interpret ProADM cutoffs and about the results from previous trials when ProADM was used in patients with LRTI [12,29,31,34,35,49-51]. ProADM is measured in an ethylenediaminetetraacetic acid (EDTA) plasma by a sandwich immunoassay (MR-ProADM, BRAHMS AG, Hennigsdorf, Germany) with an analytical detection limit of 0.08 nmol/l and a functional assay sensitivity of 0.12 nmol/l. It is available within 1.5 h upon ordering (24 h a day, daily).

Reassessment of the possibility for discharge from the acute-care hospital is based upon reaching medical stability at any time plus appropriate ProADM levels with particular emphasis on assessment on day 3 (Figure 4). On day 3, the treating physicians receive recommendations regarding discharge according to the clinical stability algorithm. Guidelines are displayed on handouts given to the treating physicians. Algorithm compliance is controlled by the study team and reasons for non-compliance are documented.

Discharge planning based on the biopsychosocial risk at admission (PACD ≥ 8) is initiated immediately and any need for action discussed at each round.

Patients with low medical risk or medically stabilized but high biopsychosocial requirements can be triaged to nurse-led care. The nursing staff is in charge of further management with medical input only at further request or if there is a medical deterioration.

Medically stable patients not fulfilling medical criteria and biopsychosocial, functional and organizational overruling criteria (see section “Overruling criteria for antibiotic treatment and hospitalization”) are considered suitable for discharge to home. Patients meeting biopsychosocial or functional overruling criteria and organizational criteria (waiting for a transfer to the non-acute setting) are referred to non-acute medical care (nurse-led care, health resort, rehabilitation, transitional care or long-term care) (Figure 4).

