C. Functional status (defined by SPI, activities of daily living and instrumental activities of daily living) and adverse events (that is the recurrence rate at 30 days, rate of complications (acute renal failure, ICU requirement, nosocomial infections or medication side effects), delirium, falls or pressure ulcers). Our hypothesis is that there is no difference in the functional status achieved 30 days after inclusion between the two groups.

D. Patient satisfaction with the provided service and quality of care at 30 days and 90 days.

E. Healthcare-related quality of life at the day of discharge as measured with the EQ-5D questionnaire. The hypothesis for D and E is that there is no difference in patient satisfaction and health-related quality of life between the intervention and the control groups.

F. We will describe the effective and chargeable costs for the entire treatment pathway in an exploratory economic analysis.

Endpoints will be assessed at hospital discharge, and 30 and 90 days after admission. An adverse event in a subject is defined as any untoward occurrence of any unfavorable and unintended clinically relevant medical sign, any symptom or any disease temporally associated with the study, which must not necessarily have a causal relationship with the study procedure. Any serious unexpected adverse event (for example, transfer to ICU, re-hospitalization, recurrence of an UTI, papillary necrosis, intrarenal or perirenal abscess, emphysematous pyelonephritis, allergic reaction to contrast medium during ultrasound or death) within 180 days after study inclusion is monitored by the data safety and monitoring board (DSMB). All adverse events will be followed until resolution, until the condition stabilizes, until the event is otherwise explained or the subject is lost to follow-up.

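### Day-30 functional status is compared without adjustment although the PACD is taken on admission in all patients; prespecifying it as a covariate would gain precision of unknown, possibly small, size

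*Protocol article*

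**What the plan says.** The protocol article, under Outcomes and adverse events, lists as secondary endpoint C of Intervention B: "Functional status (defined by SPI, activities of daily living and instrumental activities of daily living". It then states: "Our hypothesis is that there is no difference in the functional status achieved 30 days after inclusion between the two groups".

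Under Analysis of secondary endpoints, the main comparison for both interventions is fixed: "the secondary endpoints will be compared by the *t*-test if normally distributed, by the Mann–Whitney *U* test if similarly shaped". Adjusted models follow as a further step: "Exploratory analyses of endpoints adjusted for possible confounders will be performed using linear or logistic regression or Cox proportional hazards models". No covariates are named there. The same section says "Since this is a feasibility study we will not have enough power to test for non-inferiority" and "Estimates of effect size and corresponding confidence intervals will be provided".

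On what is measured at entry, the Intervention B section says of the PACD that it "is used to stratify all patients as low or high risk for subsequent rehabilitation and care". This describes risk classification for care planning; the Randomization section names no stratification factor. The text after Figure 4 places the score on admission: "Discharge planning based on the biopsychosocial risk at admission (PACD ≥ 8) is initiated immediately".

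**The concern.** Part of the rationale for Intervention B is that hospital stays can cost older patients their independence. Day-30 function is where the trial compares the arms on that. The expected answer is no difference, formal non-inferiority is ruled out for lack of power, and effect estimates with intervals are promised instead. The reader's conclusion will therefore rest on how wide the interval is.

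Eligible patients are any adults from the community or a nursing home, and the overruling criteria foresee dementia, falls and limited mobility. Much of the spread in day-30 function is plausibly present before randomization. An unadjusted test leaves that spread in the error term.

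Calling the covariates possible confounders also misplaces the purpose. In a randomized comparison the benefit of a baseline covariate is precision. Leaving the set unnamed has a risk: the corresponding list for the primary endpoint, under Statistical considerations, includes time to stability, which arises after randomization.

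**Working it through.** **The protocol's own figure.** For Intervention B the Sample size section gives 112 per arm for 6 versus 4.5 days, SD 4, 80% power and 5% alpha. With a two-sided test, n = 2(1.960 + 0.842)² × 4² / 1.5² = 2 × 7.85 × 16 / 2.25 = 111.6, so 112. This reproduces. The protocol gives no SD, sample size or precision for functional status, so the rest is in units of the outcome SD.

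**Inputs.**
- Evaluable patients: the Abstract plans 250 enrolled with 20% loss, so 250 × 0.8 = 200. With 1:1 allocation that is n = 100 per arm.
- Correlation r between the admission score and day-30 function: not in the protocol. It is an assumption, varied from 0 to 0.7.

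**Unadjusted 95% half-width.** t(0.975; 2n − 2) × √(2/n) = 1.972 × √(2/100) = 1.972 × 0.1414 = 0.279 SD.

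**Half-width with one baseline covariate in a linear model.** t(0.975; 2n − 3) × √(2/n) × √(1 − r²) × √(1 + 1/(2n − 4)). The last factor is the small price of estimating the slope: √(1 + 1/196) = 1.0025. The number of patients per arm that would give the same precision unadjusted is about n/(1 − r²).

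| r | Adjusted half-width (SD) | Change | Equivalent patients per arm |
|---|---|---|---|
| 0 | 0.280 | +0.3% | 100 |
| 0.2 | 0.274 | −1.8% | 104 |
| 0.3 | 0.267 | −4.4% | 110 |
| 0.5 | 0.242 | −13.2% | 133 |
| 0.7 | 0.200 | −28.4% | 196 |

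The percentages are almost the same at 112 or 125 per arm.

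**Ceiling.** The population includes simple UTI and outpatients, so many patients may score at the top of a function scale. A simulation with 100 per arm and 3,000 runs capped outcome and covariate at 0.3 SD above the mean, with no arm effect. The interval then narrowed by about 3%, 10% and 24% at underlying r = 0.3, 0.5 and 0.7. Coverage stayed at 95% to 96%.

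**Score reduced to low or high risk.** In the same simulation, a two-category covariate (cut at 0.5 SD below the mean) narrowed the interval by only about 2%, 7% and 16%. The score should therefore enter as a continuous covariate.

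**What is measured in everyone.** The outcome instruments are SPI, ADL and IADL. The article does not say that any of these is scored in every patient at entry. Under Overruling criteria the SPI carries a note that it applies during the hospital stay, and the Intervention B section uses it to judge fitness for discharge. The PACD is the only score the article applies to all patients, and it is not one of the outcome instruments.

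**The case against.** The strongest reply is that nothing in the section is wrong. A t-test or Mann–Whitney test in a randomized trial is valid, estimates with intervals are promised, adjusted regressions are already planned, and covariates for a secondary endpoint are commonly named in an analysis plan that is not shown. Function is also not the only check on earlier discharge: re-hospitalization, complications, falls, delirium and pressure ulcers are tracked too. Validity and the other checks stand, and they limit how serious the point is. The reply does not remove it, because the article chooses the unadjusted test as the main comparison and ranks adjustment as exploratory. That is a stated choice and not an omission.

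Several stronger readings are tempting, and the document does not support them:

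- A reader might infer that function itself is scored in every patient on admission, so that adjustment is free. Only the PACD is described for all patients, and the article does not say whether it is scored before allocation.
- A reader might want to add the admission SPI wherever it is recorded. As described, the SPI belongs to the hospital stay, which Intervention B is designed to change. Whether it is recorded could depend on the arm, and a model restricted to patients who have it could drop outpatients selectively and bias the comparison.
- A reader might take correlations of 0.5 to 0.8 as the working range. Nothing in the article supports these values, and low ones are plausible for a score that is a different instrument from the outcome.
- A reader might count chance baseline imbalance as a second defect. The unadjusted interval already covers it, so it is the same precision point again.

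**Conclusion.** The point holds as a gain in precision and not as the correction of an error. The main comparison of day-30 function is unadjusted although the PACD is available on admission in all patients. Prespecifying it as a covariate would narrow the 95% interval by about 2%, 4%, 13% and 28% at r = 0.2, 0.3, 0.5 and 0.7, and by less if the score has a ceiling. If the PACD turned out to be unrelated to day-30 function, the interval would widen by about 0.3%.

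This rests on three assumptions: about 100 evaluable patients per arm, a correlation that the article does not report, and a PACD scored before or independently of allocation. Since the PACD is not an outcome instrument, the lower part of the range may be the realistic one. The case for the change is that the possible loss is negligible and that this endpoint depends on its interval.

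**What to change.** Under Analysis of secondary endpoints, name the main analysis of day-30 functional status as a prespecified linear or proportional-odds model on the randomized triage arm, with admission PACD as a continuous covariate. Keep the unadjusted test as a sensitivity analysis.

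Two conditions belong with it. First, the sponsor should confirm that the PACD is scored before allocation or independently of it. Second, the model should not adjust for an SPI recorded only during hospitalization. Baseline SPI, ADL or IADL should be added only if already taken in every patient before allocation.

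The cost is a sentence or two in the analysis section. No further patients are needed, and if the PACD condition is met, no further data either. Starting to collect SPI, ADL or IADL at entry would be additional work and is not part of this request.

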## Discussion

The results of earlier studies by our group provided evidence that antibiotic therapy can be guided in patients with LRTI using PCT cutoff ranges. We recently showed that biomarkers, especially ProADM, are able to predict the outcome for patients with LRTIs [58]. On account of this, we added the ProADM to the widely used CURB65 score, resulting in the CURB65-A score capable of guiding triage decisions [31,35].

In this study we extend our concepts to patients with UTI, which contributed approximately 7% of patients in the previous French multi-center ProRATA study [13]. UTIs, as one of the most common indications for antibiotic therapy [59], provide an ideal opportunity for extrapolating our knowledge from LRTI studies.

In the current guidelines [4,10,19] a crucial point in the determination of the length of antibiotic therapy and whether a patient has to be hospitalized or not, has been the distinction between lower and upper UTI, and this classification is still based on subjective criteria. The first aim of this study is to create evidence-based guidelines, which will allow clinicians to administer tailored antibiotic therapy in uncomplicated as well as in complicated UTIs by using PCT levels and pyuria dynamics. This will help to determine the optimal length of antibiotic therapies and avoid antibiotic overuse.

As shown in a study among a population of frail elderly nursing home residents, 43% of all patients receiving antibiotic treatment for an assumed UTI are over-diagnosed and actually do not require antibiotics [60]. Another large potential for reducing antibiotic use lies in febrile UTI patients, who currently receive at least 7 days of antibiotics according to guidelines.

The second aim is to support clinicians in site-of-care decision-making, for which we will use the ProADM cutoff levels we extracted from our previous trials [29,31,35,36]. This study can provide proof of our concept, in that the algorithms we obtained in our LRTI studies can be adapted to other common infections with only minor disease-specific adaptations. Given the fact that UTIs have a high prevalence, any improvement to the current risk assessment is of both great socio-economic and scientific interest. Hospital stays are very costly and avoiding or shortening the LOS could result in large savings [61]. Clinical severity scores classify patients according to the presence of co-morbidities and subjective criteria [45]. Even though recommended in guidelines, these clinical scores have the disadvantage of being too general and do not give sufficient weight to the host response [50,62]. Adding objective criteria such as easily measurable biomarkers to these clinical scores individualizes medical decisions and might detect subgroups that have a higher risk of suffering complications and therefore require increased attention and particular care. On the other hand, a trustworthy method of identifying patients with a low risk of adverse events, allows outpatient treatment with lower risk of healthcare-associated infections [63], as well as treatment in nurse-led care. It gives physicians, nurses, patients and relatives the required confidence in their decisions. Risk-based triage could reduce bed shortages during peak times and lead to lower costs.

### Potential limitations

This protocol describes two randomized open intervention trials in one factorial study design with an expected high external validity. However, contamination within the proposed open trial design is obvious. The Hawthorne effect of an earlier discharge in the intervention group compared to the control group is possible as well as a spillover effect since PCT and ProADM values are not blinded because they are part of the routine chemistry. However, the bias due to the Hawthorne effect for the primary endpoints (for Interventions A and B) is expected to be conservative and favor the null hypothesis. The research team emphasizes treatment and triage algorithms according to the randomized group. Previous studies showed poor guideline compliance despite high-intensity implementation. Therefore the expected spillover effect will also have a conservative influence on the primary endpoints. We minimize ascertainment bias by having objective, measurable primary endpoints. More subjective secondary endpoints will be assessed by blinded researchers.

## Abbreviations

Abx: Antibiotics; CAP: Community acquired pneumonia; CEUS: Contrast-enhanced ultrasound; cfu: Colony-forming unit; CRP: C-reactive protein; DSMB: Data safety and monitoring board; ED: Emergency department; EDTA: Ethylenediaminetetraacetic acid; GFR: Estimated glomerular filtration rate with MDRD formula; ICU: Intensive care unit; LOS: Length of stay; LRTI: Lower respiratory tract infection; NSAIDs: Nonsteroidal anti-inflammatory drugs; PACD: Post-acute care discharge score; PCT: Procalcitonin; ProADM: Proadrenomedullin; PSA: Prostate-speicifc antigen; SPI: *Selbstpflegeindex* self-care deficit score; TMP-SMX: Trimethoprim-sulfamethoxazole; UST: Urinalysis; UTI: Urinary tract infection
